### Statistical considerations

#### Sample size

Sample size calculation was based on a two-sided α error of 0.05 and a 80% power (β). On the basis of our experience, we anticipate that the 50% of patients with ventilation cessation during CPB and no PEEP before and after CPB will reach the composite endpoint of EFL after CPB and respiratory complications at 5 days, while only the 30% of the patients treated with an optimal ventilatory strategy will develop this composite endpoint. Including a drop-out fraction of 10%, we will enroll 51 patients per group, 204 in total.

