### Objectives

EFL occurs when, at a given lung volume, the expiratory flow is independent of the patient’s expiratory effort or on an increase of elastic recoil pressure [13]. The purpose of this study is to investigate whether an optimal lung recruitment strategy before CPB, based on a best PEEP calculated according to the PEEP test, and during CPB, with a continuous positive airway pressure (CPAP) instead of no ventilation, would reduce the incidence of the EFL phenomenon and of PPCs after cardiac surgery, compared with no PEEP before, during, and after CPB.

The main hypothesis of this trial is that an adequate lung recruitment based on the best PEEP before and after CPB, defined as the minimum PEEP level necessary to avoid the EFL phenomenon, and/or an adequate level of CPAP during could reduce lung injury following cardiac surgery.

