## Methods/design

### Trial design

This will be a single-center, single-blind, parallel-group, randomized controlled trial. Using a 2-by-2 factorial design, high-risk adult patients undergoing elective cardiac surgery will be randomly assigned to receive either a best PEEP (calculated with a PEEP test) ventilation or a zero PEEP strategy before and after CPB and CPAP (equal to the best PEEP) or no ventilation (patient disconnected from the circuit) during CPB.

We will recruit all patients that will match the eligibility criteria at the preoperative evaluation. The protocol structure was written in according to the Consolidated Standards of Reporting Trials (CONSORT) 2010 Statement [14] and follows the Standard Protocol Items: Recommendations for Interventional Trials (SPIRIT) Statement [15]. The SPIRIT Figure of this trial is illustrated in Fig. 1. The SPIRIT Checklist of this trial can be found in Additional file 1. Patients will also be evaluated in terms of (1) shunt fraction and (2) data of respiratory mechanics, such as static compliance, flow, and additional resistance. All these parameters will be determined: (1) immediately after anesthesia induction, (2) before CPB, (3) during CPB, (4) off pump, and (5) end of surgery.

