#### Data analysis

A statistical consultant dedicated, but not involved in patient management, will provide independent consultancy for data-quality checking and statistical analysis, and will be responsible for the statistical analysis. Data will be analyzed by means of SPSS 25.0 software. All data analyses will be carried out according to a pre-established intention-to-treat analysis plan. In addition, per-protocol analyses will be carried out, but only as a means to explore safety and feasibility. We will analyze patients in the treatment group to which they are allocated. Two-sided significance tests will be used. Dichotomous variables will be analyzed using the two-tailed ***χ***^2^ test, using the Yates’ correction when appropriate. Continuous variables will be compared by analysis of variance or the non-parametric Kruskal-Wallis test. Relative risks with 95% confidence intervals and differences between medians with 95% confidence intervals (using the Hodges-Lehmann estimation) will be calculated when appropriate.

The principal comparison will be between the patients who will or will not receive best PEEP ventilation and who will or will not receive CPAP during CPB.

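### The sample size is right for 50% vs 30% between the two levels of a factor, but the text gives those rates to opposite cells of the 2-by-2, where 80% power cannot hold for both factors

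*Protocol article*

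**What the plan says.** The Trial design section of the protocol article describes a factorial trial: "Using a 2-by-2 factorial design, high-risk adult patients undergoing elective cardiac surgery will be randomly assigned" to a PEEP factor (before and after bypass) and a CPAP factor (during bypass). The section on interventions adds that the two randomizations are independent.

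The Sample size section uses a two-sided 5% level and 80% power. It anticipates that "the 50% of patients with ventilation cessation during CPB and no PEEP before and after CPB will reach the composite endpoint", while "only the 30% of the patients treated with an optimal ventilatory strategy will develop this composite endpoint". It concludes: "Including a drop-out fraction of 10%, we will enroll 51 patients per group, 204 in total".

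The Data analysis section then says: "The principal comparison will be between the patients who will or will not receive best PEEP ventilation and who will or will not receive CPAP". It plans a two-tailed chi-square test for dichotomous outcomes, with Yates' correction when appropriate. No rates are given for patients who receive only one of the two interventions.

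**The concern.** The 50% is attached to patients who lack both interventions, which is one cell of the 2-by-2. The 30% is attached to an optimal strategy, which the Sample size section does not define but which most naturally means both interventions, the opposite cell. The principal comparisons are between margins: all patients with a factor against all patients without it, averaged over the other factor. A difference between opposite cells is the combined effect of two factors. A marginal difference is the effect of one.

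If cell rates were used to size marginal comparisons, the trial could be much less sensitive to each factor than its 80% suggests. The Discussion says the factorial design is there to separate what happens during bypass from what happens before and after it. A non-significant result on one factor would then be judged against a power that the printed rates do not support.

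**Working it through.** **Inputs.** Rates 50% and 30%, two-sided alpha 0.05, power 80%, drop-out 10%, 51 per group and 204 in total (Sample size); four cells (Trial design); marginal principal comparisons and chi-square test (Data analysis). The rates in the two single-intervention cells are not given, so a range is shown.

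**1. Reproducing 204.** With pooled variance under the null,

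n = [1.960·√(2·0.40·0.60) + 0.842·√(0.50·0.50 + 0.30·0.70)]² / 0.20² = 93 per compared group.

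93 × 1.1 = 102.3, so 102 per compared group, which is 2 × 51; two such groups make 204. Dividing by 0.9 instead gives 186/0.9 = 207 in total, also close. The figure therefore fits a comparison of 102 vs 102, that is, one margin against the other. A contrast between two cells would need 93 evaluable patients per cell, not 51 enrolled.

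**2. A constraint that needs no further assumption.** Write p00 for neither, p10 and p01 for one intervention only, p11 for both. With equal cell sizes the marginal differences are

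- PEEP: (p00 + p01)/2 − (p10 + p11)/2
- CPAP: (p00 + p10)/2 − (p01 + p11)/2

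Their sum is p00 − p11, because the single-intervention cells cancel. With p00 = 50% and p11 = 30% the sum is 20 points, so the two differences average 10 points whatever the interaction. They cannot both be 20.

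**3. Power.** Exact enumeration of the uncorrected chi-square test. After 10% drop-out, 51 × 0.9 ≈ 46 per cell and 102 × 0.9 ≈ 92 per margin.

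| Assumption | Contrast | Power after drop-out |
|---|---|---|
| Both vs neither | 50% vs 30%, 46 per cell | 49% (56% with all 51) |
| Equal split, cells 50/40/40/30 | 45% vs 35%, each margin | 28% per factor (32% with all 102) |
| 15/5-point split | 47.5% vs 32.5%; 42.5% vs 37.5% | about 55% and 10% |
| One factor carries everything | 50% vs 30%; 40% vs 40% | 79% and 5% (the error rate) |
| Either intervention alone, or both, gives 30% | 40% vs 30%, each margin | 30% per factor |
| 50% and 30% are marginal rates | 50% vs 30%, each margin | 79% per factor (84% with all 102) |

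Multiplicative rather than additive effects also give about 28% in the equal-split case. Yates' correction lowers the figures: 49% becomes 41%, 28% becomes 23%, and 79% becomes 75%.

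**4. What the marginal reading implies.** If both margins are 50% vs 30%, the sum in step 2 is 40 points, so p00 − p11 = 40 points. If the neither cell is at the printed 50%, the cell with both would have to be at 10%, not 30%.

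**The case against.** The strongest reply is that 50% and 30% were meant as the rates at the two levels of each factor. That reading reproduces 204, matches the principal comparisons and gives close to 80% for both. A reader might infer from the cell wording that no reading supports the stated power, or that 204 is an arithmetic error. Neither inference is supported: the arithmetic is correct, and the marginal reading delivers the power. But it is not what the text says, since the 50% is tied to patients who lack both interventions. If it was intended, the rates are attached to the wrong groups and the sentence still needs correcting.

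A second reply is that 28% cannot be derived from the article, because the single-intervention rates are missing. This stands: 28% is the equal-split case, and on the cell reading single-factor power runs from about 5% to 79%. What does not depend on the split is that both factors cannot reach 80%.

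A reader might also see a contradiction between the Objectives, which set the combined strategy "compared with no PEEP before, during, and after CPB", and the marginal comparisons. That goes too far. The next paragraph of the Objectives states the hypothesis for either intervention or both, which fits a factorial analysis.

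Finally, relative risks with 95% confidence intervals are planned, so a null result would show its own imprecision. That softens the consequence but does not correct the power statement. Nor is this detail left to an analysis plan: the rates, the size, the power and the principal comparison are all printed, and they do not fit together.

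**Conclusion.** The point holds as a mismatch between the assumed rates and the comparisons that the size serves. On the natural reading of the Sample size section (50% with neither intervention, 30% with both), 80% power for both principal comparisons is impossible, with no assumption beyond equal cell sizes. How far power falls depends on the unstated split: after drop-out, about 28% per factor if equal, 55% and 10% for a 15/5 split, 79% and 5% if one factor does all the work. Both against neither has about 49%. Reading the optimal strategy as any active arm does not rescue the claim (about 30% per factor). The stated power is right, at about 79%, only if 50% and 30% are marginal rates for each factor. These figures assume 10% drop-out spread evenly and an uncorrected chi-square test.

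**What to change.** Keep 204 patients and correct the Sample size section in one of two ways.

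- State that 50% and 30% are the expected rates at the two levels of each factor, averaged over the other, with about 80% power per factor. The description of the 50% group must change accordingly, and the sponsor should check that the implied 40-point gap between neither and both is credible.
- Keep 50% and 30% as cell rates, list all four assumed cell rates, and replace the 80% with the power those rates give for each principal comparison in the Data analysis section (about 28% per factor under an equal split).

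Either way the cost is wording, and the article says recruitment has not started. The second option makes the stated power less favourable. For scale only: 80% for both margins under an equal split would need 376 evaluable per margin, 752 in total, which is not asked for here.

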#### Data analysis

A statistical consultant dedicated, but not involved in patient management, will provide independent consultancy for data-quality checking and statistical analysis, and will be responsible for the statistical analysis. Data will be analyzed by means of SPSS 25.0 software. All data analyses will be carried out according to a pre-established intention-to-treat analysis plan. In addition, per-protocol analyses will be carried out, but only as a means to explore safety and feasibility. We will analyze patients in the treatment group to which they are allocated. Two-sided significance tests will be used. Dichotomous variables will be analyzed using the two-tailed ***χ***^2^ test, using the Yates’ correction when appropriate. Continuous variables will be compared by analysis of variance or the non-parametric Kruskal-Wallis test. Relative risks with 95% confidence intervals and differences between medians with 95% confidence intervals (using the Hodges-Lehmann estimation) will be calculated when appropriate.

The principal comparison will be between the patients who will or will not receive best PEEP ventilation and who will or will not receive CPAP during CPB.

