### Interventions (randomization and treatment protocol)

Once the patient has provided informed consent, the investigator (e.g., the anesthesiologist in the operating theater) logs into a dedicated on-line portal (www.eflvent.it) to obtain the allocation arms. The randomization will be in a 1:1 ratio between the parallel groups, in blocks of 20 patients. From that moment, the online data will be anonymous and, in any event, the patient will be analyzed according to the “intention-to-treat” principle.

To reduce the bias, data will be collected by trained observers, trained accordingly to Good Clinical Practice (GCP) guidelines [16, 17], who will not participate to patient care. Furthermore, we decided to focus on clinically relevant data that cannot be influenced by physician management. Caregivers will be interviewed daily about the occurrence of postoperative adverse events. The patients will be blinded to the allocation arm.

All patients will receive lung protective ventilation, with a tidal volume of 7 ml/Kg of ideal body weight (IBW), a respiratory frequency titrated to maintain normocapnia, assessed by seriated blood-gas analyses. FiO_2_ will never be higher than 80%, except for the blood samples obtained for shunt fraction calculation.

Patients will be randomized, immediately before surgery, to receive either a PEEP equal to the best PEEP, assessed with a PEEP test, immediately after the induction of anesthesia or to zero. All patient will be furthermore randomized to receive either a CPAP equal to the best PEEP or a zero PEEP strategy (with disconnection from anesthesia circuit) during CPB. The two randomizations will be independent each from other.

During CPB our goal will be to maintain PaO_2_ between 200 and 250 mmHg in order to avoid hyperoxia-induced lung injury; moreover, the hematocrit will be maintained above 24% [18].

During weaning from CPB we will perform a single alveolar recruitment maneuver (RM). This RM will be performed manually by the anesthesiologist with a gas mixture of oxygen and air (with an inspired oxygen fraction lower than 80%) at the end of procedure. After CPB, this RM will be performed manually, in correspondence to the surgical de-airing procedure. Airway pressure will be kept at 40 cmH_2_O for at least 10 s. The flowchart in figure 2 (Fig. 2) resume the enrollment and allocation process.

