### Intraoperative monitoring

Intraoperative monitoring will include: electrocardiogram (ECG), pulse oximeter, capnography, urine output, invasive blood pressure measurements, advanced hemodynamic monitoring (pulmonary artery catheter (PAC)/transesophageal echocardiogram (TEE)), bladder or esophageal temperature, and activated clotting time (ACT).

The anticoagulant protocol in our center is as follows: heparin (3 mg/Kg) to achieve an ACT of 200 s for cannulation and 480 s to proceed with the CPB. At the end of the CPB, protamine (3 mg/Kg) is used (ACT target < 150). In case of allergy to heparin, we will administer bivalirudin.

During CPB, pump flow of 2.5 L/min/m^2^ and mild hypothermia (31–33 °C) will be applied.

The following ventilatory parameters will be monitored: TV, PEEP, FiO_2_, peak airway pressure (Paw), and plateau pressure (Pplat).

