### Trial organization

The IRCCS San Raffaele Scientific Institute is the center for this study. It is responsible for the organization of the trial, development of the randomization scheme, study database, data consistency checks and analysis.

We will create an on-line platform (http://www.eflvent.it) where investigators can electronically randomize every patient and load data in the online CRF. All data will be collected anonymously in the on-line database.

Definitions and use of outcome measures are in accordance with the standards for European Perioperative Clinical Outcome (EPCO) definitions [24].

Safety monitoring activities will be performed by an independent monitoring body, with known experience in the field, and will include reviewing the protocol, data integrity, participant risk and safety; in particular, monitoring adverse events, and data confidentiality. The monitoring body will be separate and independent from the clinical staff or anyone responsible for patient care. The monitoring body will not have scientific, financial, or other conflict of interest related to the trial. Current or past collaborators or associates of the principal investigator will not be a part of the monitoring body. The monitors will follow the Declaration of Helsinki and GCP guidelines. Clinical monitors will verify adherence to required clinical trial procedures and confirm accurate collection of data. Study monitoring and follow-up, from the initial set-up to final reporting, are all fulfilled according to current national and international requirements.

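### The per-protocol analyses are assigned to exploring safety and feasibility, where a set selected on adherence can understate harm and cannot measure delivery

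*Protocol article*

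**What the plan says.** The Data analysis section fixes the main approach first: "All data analyses will be carried out according to a pre-established intention-to-treat analysis plan". It then gives the per-protocol analyses their role: "In addition, per-protocol analyses will be carried out, but only as a means to explore safety and feasibility". The next sentence returns to analysis by allocation: "We will analyze patients in the treatment group to which they are allocated". The Interventions section makes the same commitment from the moment of randomisation: "the patient will be analyzed according to the “intention-to-treat” principle".

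The article does not define the per-protocol set. Apart from the general intention-to-treat statement, the per-protocol sentence is the only one in the analysis section that mentions safety or feasibility.

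Oversight during the trial is described under Trial organization: "Safety monitoring activities will be performed by an independent monitoring body", with a remit that includes, "in particular, monitoring adverse events, and data confidentiality". On adherence, the same section says: "Clinical monitors will verify adherence to required clinical trial procedures and confirm accurate collection of data".

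**The concern.** Adherence to a ventilation strategy is settled after randomisation, and tolerance can influence it. If the allocated strategy is reduced, abandoned or crossed over because the patient does poorly, that patient is among the likeliest to leave a per-protocol set. Harm counted in the remaining patients can then be too low, and the comparison is no longer the randomised one.

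Feasibility raises a simpler difficulty. If it means how often the allocated strategy could be carried out, it has to be counted among everyone allocated to it. Counted among patients who adhered, it comes out near 100% whatever happened in the operating theatre.

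Both questions matter here. The patients are selected for high risk of respiratory dysfunction, one level of the first factor is zero PEEP, and one level of the second is CPAP during bypass. The Limitations section itself gives haemodynamic stability as a reason for restricting recruitment to a single manoeuvre. The abstract's discussion presents the approach as simple and feasible. A per-protocol table labelled as the safety and feasibility result could be read as support for that description without being able to test it.

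**Working it through.** The plan gives no figure on this point. The check compares the sections and then works an example on assumed inputs.

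**1. What the sections cover**

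| Item | Where it stands | Patients counted |
|---|---|---|
| Pulmonary complications, including pneumothorax, respiratory failure and bronchospasm | Endpoints, Table 2 (part of the primary composite) | Intention-to-treat |
| Re-intubation, non-invasive ventilation, MACE, infections, ICU readmission, mortality | Endpoints (secondary) | Intention-to-treat |
| Adverse events and adherence during conduct | Trial organization | Monitored separately; no reporting denominator given |
| Safety and feasibility as named analysis aims | Data analysis | Per-protocol named |
| Intraoperative intolerance; delivery of the allocated strategy | Not listed under Endpoints | Not clearly reached by the intention-to-treat analysis of the endpoints |

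The gap is in the last two rows.

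**2. Denominator**

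The Sample size section gives 51 patients per group and 204 in total. Each level of a factor in the 2-by-2 design combines two groups: 2 × 51 = 102.

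**3. Feasibility (assumed number of failures)**

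Suppose the allocated strategy is not maintained in 10 of 102 patients at one factor level.

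- All randomised: 92/102 = 90.2% delivered.
- Per protocol: 92/92 = 100% delivered.

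The second result is the same for any number of failures, so the per-protocol figure carries no information on delivery.

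**4. Safety (all inputs assumed)**

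Let f be the non-adherent fraction, b the event risk in adherent patients and q the event risk in non-adherent patients.

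- Rate in all randomised patients = (1 − f)·b + f·q
- Rate per protocol = b
- Understatement = f·(q − b)

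With b = 5% and 102 patients:

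| f | q | All randomised | Per protocol | Events, all randomised | Of these, in excluded patients |
|---|---|---|---|---|---|
| 5% | 30% | 6.25% | 5% | 6.4 | 1.5 |
| 5% | 50% | 7.25% | 5% | 7.4 | 2.6 |
| 10% | 30% | 7.5% | 5% | 7.7 | 3.1 |
| 10% | 50% | 9.5% | 5% | 9.7 | 5.1 |
| 20% | 30% | 10.0% | 5% | 10.2 | 6.1 |
| 20% | 50% | 14.0% | 5% | 14.3 | 10.2 |

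Example, f = 10% and q = 30%: 0.90 × 0.05 + 0.10 × 0.30 = 0.075. The excluded events are 102 × 0.10 × 0.30 = 3.1.

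The direction depends on q being larger than b. If q equals b, the rate is not biased. The result is attenuation whose size the documents do not determine.

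**The case against.** The strongest reply is that the sentence restricts the per-protocol analysis, not the safety analysis. The word only limits what per-protocol results may be used for. They come in addition to an intention-to-treat plan for all data, and the grouping by allocation is repeated straight afterwards. This stands. A reader might infer that safety will be examined per protocol alone, so that harm is hidden and adherence cannot be seen. The documents do not support that. The main harms are listed endpoints counted by allocation, an independent body watches adverse events, monitors check adherence, and ventilatory parameters are recorded. What monitoring does not settle is the denominator for the reported safety and feasibility results, and the only set named for those two aims is per-protocol.

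Second, the set is undefined, and its definition may sit in an analysis plan that is not shown. Who would be excluded is therefore inferred from the ordinary meaning of the term. The article does not list reasons for which PEEP or CPAP might be changed. This also stands and limits what can be said on safety. It does not rescue feasibility, since a set selected on adherence cannot measure adherence.

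Third, where the article discusses feasibility it mostly means the PEEP test. On that reading the difficulty remains for the arms that need a best-PEEP value: a patient in whom the test could not be completed could not be given the allocated level, and would probably leave the set.

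Fourth, looking at patients who received an intervention can reveal harm that non-receivers dilute. That is a fair reason for a supplementary analysis by strategy received. It is no reason to drop patients who deviated.

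**Conclusion.** The point holds in a limited form. The article chooses an analysis set for exploring safety and feasibility. Under its usual meaning, that set can understate harm and cannot measure how often the allocated strategy was delivered.

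The consequence is modest. The primary comparison, the sample size and the intention-to-treat analysis of the listed endpoints are unaffected, and harm is not hidden overall. It would be too much to say that every arm is biased towards looking safe: that needs non-adherent patients to have the higher event risk, which the documents neither state nor exclude. An example that counts withdrawal of the strategy as the harm and then removes those patients gives zero by definition, so it says nothing about the bias for other events.

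The feasibility part rests only on per-protocol meaning selection on adherence. The safety part rests on that and on the assumed risks. Across the assumed range, the understatement runs from 1.25 percentage points (6.25% against 5%) to 9 (14% against 5%).

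**What to change.** Replace the per-protocol sentence in the Data analysis section with wording to this effect:

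- Safety is reported in all randomised patients by allocated arm, with a supplementary presentation by strategy received.
- Feasibility is reported as the proportion of all randomised patients in each arm in whom the allocated PEEP and CPAP strategy was delivered and maintained, with reasons for deviation.
- A per-protocol analysis, with its exclusions defined beforehand, is used only as a sensitivity analysis of the primary endpoint.

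The cost is small. PEEP and other ventilatory parameters are already monitored during surgery (Intraoperative monitoring) and collected (Data collection), and caregivers are already asked daily about postoperative adverse events (Interventions). The additions are a field on the case report form for the reason for any deviation, and one extra table. The sample size and the primary analysis do not change.

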## Discussion

Postoperative lung complications are common after cardiac surgery; when a severe complication does occur, a patient’s life may be significantly threatened.

Many factors can contribute to their development. Among these, the phenomenon of the expiratory flow limitation (EFL) has not been studied in the literature, especially in elective cardiac surgery. This phenomenon seems to correlate with PPCs in other major surgical fields and it could be easily prevented by the choice of an adequate PEEP level. Our commitment to this study has focused particularly on investigating whether optimal lung recruitment before, during and after CPB, associated with protective lung ventilation, would reduce the lung damage in cardiac surgery. The factorial trial design we decided to apply is aimed at distinguishing between what happens during CPB (e.g., lung collapse if no CPAP is applied and inflammatory damage) and before and after CPB (e.g., derecruitment and atelectrauma, without an adequate PEEP level).

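### The named tests leave out the other randomised factor, allow a Yates correction that the sample size did not use, and do not say whether margins or four groups are compared

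*Protocol article*

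**What the plan says.** The Trial design section sets out the structure: "Using a 2-by-2 factorial design, high-risk adult patients undergoing elective cardiac surgery will be randomly assigned" to best PEEP or zero PEEP before and after bypass, and to CPAP or no ventilation during bypass. The Interventions section adds: "The two randomizations will be independent each from other". The Discussion gives the reason for the design: "The factorial trial design we decided to apply is aimed at distinguishing between what happens during CPB", as opposed to before and after it.

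The Data analysis section names a two-tailed chi-square test for dichotomous outcomes, "using the Yates’ correction when appropriate". For continuous outcomes it says: "Continuous variables will be compared by analysis of variance or the non-parametric Kruskal-Wallis test". The effect measures are relative risks and Hodges-Lehmann differences. Its last sentence makes the principal comparison PEEP against no PEEP and CPAP against no CPAP, which are the two main effects.

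The Sample size section uses a two-sided 5% level, 80% power, 50% against 30%, and 10% drop-out. It arrives at 51 per group and 204 in total.

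**The concern.** Three things are left loose in a section that otherwise commits to particular tests.

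- No named method is said to carry the second randomised factor, by stratification or by a model term, and no PEEP-by-CPAP contrast is mentioned.
- Yates' correction is admitted on an unstated condition. If used on the primary endpoint, the trial would be analysed with a more conservative test than the one it was sized for.
- Analysis of variance and Kruskal-Wallis are the usual pair for more than two groups, and the Sample size section speaks of groups of 51, of which there are four. A four-group comparison is therefore a possible reading. Kruskal-Wallis takes one grouping variable, so across four cells it cannot say which factor is responsible.

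At stake is power in a trial sized at 80% with little to spare. There is also a choice between tests that could be made after the data are seen.

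**Working it through.** **Inputs.** From the Sample size section: 50% v 30%, two-sided 0.05, power 0.80, drop-out 10%, 51 per group, 204 in total. Evaluable numbers: 51 × 0.9 = 45.9, taken as 46 per cell and 92 per margin. All other cell rates below are assumptions. They are listed as neither / PEEP only / CPAP only / both.

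**1. Reproducing 204.** Pooled-variance formula, no continuity correction, mean rate 0.40:

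n = [1.96·√(2·0.4·0.6) + 0.8416·√(0.25 + 0.21)]² / 0.2² = (1.358 + 0.571)² / 0.04 = 93 per margin.

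93 × 2 × 1.1 = 204.6, which matches 204 = 4 × 51. The trial is therefore sized for a margin of 102 v 102, without continuity correction. With the correction, n′ = (93/4)·[1 + √(1 + 4/(93·0.2))]² = 102.8, so 103 evaluable per margin, or about 228 to 230 enrolled. That does not match.

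**2. Yates.** Exact calculation, 92 per margin:

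| Test | Power, 50% v 30% | Actual size, 40% v 40% |
|---|---|---|
| Plain chi-square | 79.4% | 4.9% |
| With Yates | 75.0% | 3.5% |

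**3. Margin or four groups.** One factor works (cells 50/30/50/30), 46 per cell. Non-centrality = 46 × 4 × 0.1² / 0.24 = 7.67. Power is 79% on 1 df and 63% on 3 df. For a continuous outcome with an assumed 0.4 SD effect of one factor, non-centrality = 184 × 0.2² = 7.36. Power is 77% on 1 df and 60% on 3 df.

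This loss belongs to the one-factor case. If both factors work (60/40/40/20), the four-group test rejects more often (94% v 80% for one margin), but it does not attribute the effect to a factor.

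**4. Stratifying by the other factor.** Simulation, 200,000 trials per scenario, 46 in every cell:

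| Assumed cells | Plain margin | Mantel-Haenszel |
|---|---|---|
| 50/30/50/30 | 79.3% | 79.2% |
| 60/40/40/20 | 79.9% | 81.7% |
| 70/50/30/10 (extreme) | 81.6% | 86.8% |
| Size, other factor 20 points | 4.4% | 5.2% |
| Size, other factor 40 points | 3.1% | 5.0% |

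The low size has a simple cause. With a 20-point other factor, the marginal test uses a variance of 0.40 × 0.60 = 0.24, while the average within strata is (0.25 + 0.21)/2 = 0.23. This holds for equal cells. With independently drawn lists, chance imbalance adds variance back. The gap is (0.24 − 0.23) × 2/92 = 0.00022, whose square root is about 1.5 points. That is close to the 1.4-point SD found by simulating two independent block-20 lists. Averaged over such lists, the marginal test is then near its nominal size.

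**5. Interaction.** A logit-scale test at 46 per cell has about 27 to 28% power for cells 50/50/50/30 or 50/30/30/30.

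**The case against.** A reader might infer that the factorial question goes untested. The text does not support that. The principal-comparison sentence names both main effects, a chi-square on each margin tests them validly, and two main effects are what separates the bypass period from the periods around it. Only the interaction is unaddressed.

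A reader might also infer that the two independent lists let one factor's effect bias the other's. They do not. The 1.4-point shift has mean zero. Against a standard error of √(0.46/92) = 7.1 points, it is about 4% of the variance.

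The defence has further good points. Analysis of variance can be two-way, and nothing says it is one-way. On a two-level margin, Kruskal-Wallis is the Wilcoxon test. Relative risks and Hodges-Lehmann differences are two-group measures, and 204 reproduces only as a margin comparison, so margins are the likelier intention. Yates is conditional. With 92 × 0.4 ≈ 37 expected events per margin, the usual small-count reason for it is absent. Finally, the section cites a pre-established analysis plan that is not shown and that may hold the model and the interaction.

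All of this limits the point without removing it. The protocol chose to name its tests. As named, they permit a correction that the trial is not sized for and two readings with different power.

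**Conclusion.** The point holds as one of efficiency and clarity. The validity of the marginal tests is not in question.

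- Yates on the primary endpoint would cost about 4 points of power (79% to 75%).
- A four-group test would cost about 16 points (79% to 63%) when only one factor works.
- Stratifying gains 0 to 2 points in plausible cases and about 5 only if the other factor has a 40-point effect. With equal cells it also gives correct rather than conservative size.

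These figures take 50% v 30% as the contrast on one factor's margin and 10% loss. The Sample size section attaches the 50% to patients with neither intervention ("we anticipate that the 50% of patients with ventilation cessation during CPB and no PEEP before and after CPB"). If the 20 points belong to the combined strategy, all marginal power is much lower. That is a separate matter and lends no weight here.

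**What to change.** In the Data analysis section, state the following.

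- Each factor is tested on its margin with the other factor in the model. For the composite endpoint this is a Mantel-Haenszel relative risk or a two-factor binomial or logistic model. For continuous outcomes it is a two-way model, or a stratified rank test such as van Elteren where the outcome is skewed.
- No Yates correction is applied to the primary endpoint.
- The four cell rates and the PEEP-by-CPAP interaction are reported with a 95% confidence interval and labelled imprecise, given about 27 to 28% power under the assumed cells.

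The randomisation blocks need not change for this purpose. Nor should the post-induction value be added as a covariate on this ground, because it may be measured after randomisation under the allocated PEEP.

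The cost is a few sentences of wording before recruitment starts, with no additional patients.
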